### Outcome measures

At one, four, seven and thirteen months after recruitment, all participants will be contacted by telephone and consent sought for interview. Socio-demographic information will be confirmed, and all outcome instruments and mutable independent variables will be recorded (Table 1). Semi-structured questions will be asked about how participants are managing, their concerns and reasons for subsequent hospitalizations and ED presentations. At the four, seven and thirteen month data collection points (after nested RCT commencement), assessors will be blinded to group allocation.

**Table 1 T1:** Timeframes of outcome measurements

**Measures**	**Baseline**	**1 month**	**4 months**	**7 months**	**13 months**
ADLs	√	√	√	√	√
iADLs	√	√	√	√	√
SF12	√	√	√	√	√
AQoL_4D	√	√	√	√	√
Falls	√ (last 12 months)	√ (last month)	√ (last 3 months)	√ (last 3 months)	√ (last 6 months)
Hospitalizations	√ (last 6 months)	√ (last month)	√ (last 3 months)	√ (last 3 months)	√ (last 6 months)
Gait aid (type)	√	√	√	√	√
Living arrangements	√	√	√	√	√
Carer engagement	√	√	√	√	√
Organized (formal) community services	√	√	√	√	√
GP visits	√	√	√	√	√
Informal community supports	√	√	√	√	√
Satisfaction with community supports	√	√	√	√	√

ADLs, activities of daily living; AQoL_4D, Australian Quality of Life; GP, general practitioner; iADLs, instrumental activities of daily living; SF12, Short Form-12 Health Survey; √ indicates an occasion of data collection.

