### Study 1 analysis

FD will be assessed as change from baseline at each time point as:

•One or more falls increase from the baseline rate

•More than one event of hospitalization, or ED presentation, from the baseline rate

•Decrease of one point in any item of the ADL instrument [18], or

•Decrease of 2+ points from baseline total iADL score [19], or any decrease in baseline score in the domains of home activities, doing laundry, shopping and getting places (we previously reported these domains as critical to functional independence) [37]

•Scores decreasing from above median at baseline in either physical or mental domain, to below median in the SF12 [41,42]

•Any decrease in AQoL_4D (in the manner recently described for chronic obstructive pulmonary disease (COPD))[44]

•Change to a more assistive gait aid (for example, a one point stick to a four-pronged stick)

•Change in living arrangements to more supported care

•Increased carer involvement

•Greater type and frequency of use of formal community services or informal supports

•More frequent GP attendances.

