The three study cohorts will be assessed at time of allocation into a study arm (one-month after recruitment) for homogeneity in key socio-demographic characteristics and immutable factors (for example, gender, age, schooling, postcode, diagnosis) and all outcome measures (including the percentage of ‘frequent flyers’ in each arm). We previously reported this as one or more ED contacts per month over the preceding 12 months [33,34].

Change over time in each outcome measure will be calculated using repeated measures analysis of variance (ANOVA) models, with study contact point, cohort (1, 2, or 3) and key demographic features as independent variables. Partial Least Squares (PLS) models using pathway analysis will be applied to the multiple outcome, immutable and mutable independent variables at each time point, to determine different spatial arrangements and the significant factors which impact on data clusters.

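### Repeated measures ANOVA is fixed for every outcome, although at least gait aid and living arrangements are ordered categories and falls, hospitalizations and GP visits are counts

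*Protocol article*

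**What the plan says.** Under Analysis of data from Studies 1 and 2, the protocol article states: "Change over time in each outcome measure will be calculated using repeated measures analysis of variance (ANOVA) models". The terms it names for this model are the contact point, the three-level cohort and demographic characteristics. The only other method named there is partial least squares path modelling across the variables at each time point. No model for categories or counts is named.

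Table 1 ("Timeframes of outcome measurements") has 13 rows. Four are scale scores: ADLs, iADLs, SF12 and AQoL_4D. Three are naturally counts: falls, hospitalizations and GP visits. The other six are gait aid (type), living arrangements, carer engagement, formal services, informal supports and satisfaction. No measurement scale or coding is given for any of the six. The text introducing the table says that "all outcome instruments and mutable independent variables will be recorded (Table 1"), so outcomes and independent variables share one list.

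Study 1 analysis turns most of these rows into criteria for functional decline. For gait aid the criterion is "Change to a more assistive gait aid (for example, a one point stick to a four-pronged stick"); for living arrangements it is "Change in living arrangements to more supported care". Falls and hospitalizations are judged against a baseline rate.

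**The concern.** This is a stated choice of method, not a detail left open. An analysis plan that followed the sentence literally would carry the mismatch forward.

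An ANOVA compares means. For gait aid and living arrangements, a mean exists only after someone assigns numbers to the levels. The document supplies the direction of those numbers but not the distances between them. For raw counts, a mean is comparable between contacts only if each contact covers the same length of time, and here it does not.

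The affected measures are not peripheral to the conclusions. Under Hypotheses, the first hypothesis requires no decline on any measure in the observed cohort. The second is met by significant decline on a single measure in the untreated low-score cohort, judged against its own baseline. One badly modelled row could therefore decide either hypothesis.

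**Working it through.** **The plan's own figure.** The only sized quantity is the RCT sample: 50 per arm for an iADL difference of 1.2 at 80% power and 5% alpha. No standard deviation is given, so it cannot be reproduced forwards. Solved backwards (two-sided), SD = 1.2 × √(50/2) / (1.960 + 0.842) = 6.0 / 2.802 = 2.14. This concerns a scale score, for which ANOVA is a usual choice, so nothing below alters it.

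**Row count.** 4 scores + 3 counts + 6 others = 13. Of the six others, two are categories by their own description (gait aid type, living arrangements). Counts plus clear categories: 3 + 2 = 5 rows that do not fit a means model.

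**Ordered categories: what the spacing does.** Take four ordered levels.
- Codes 0, 1, 2, 3 give every step the same weight.
- Codes 0, 1, 2, 6 keep the order, but the last step counts 6 − 2 = 4.
- Codes 0, 3, 4, 5 keep the order, but the first step counts 3.

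All three agree with Study 1 analysis, and nothing in the document chooses between them.

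To see whether this matters, a group-by-time repeated measures ANOVA was run on simulated data: 2 arms of 50, 5 contacts, 2,000 data sets. All simulation inputs are assumptions: a latent normal scale with between-person SD 1.5 and within-person SD 0.5, cut at 0.3, 1.2 and 2.0, with one arm drifting by 0, 0, 0.2, 0.35 and 0.5.

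| Codes | p in one data set | Share with p < 0.05 | Verdict differs from 0,1,2,3 |
|---|---|---|---|
| 0,1,2,3 | 0.150 | 63% | – |
| 0,1,2,6 | 0.570 | 47% | 24% |
| 0,3,4,5 | 0.054 | 54% | 17% |

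Collapsed to two levels, the same data set gives p = 0.047 under either coding. The dependence on codes arises only with three or more levels.

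**Counts: what the recall windows do.** The windows come from Table 1. Expected count = annual rate × window in months / 12. At a constant one event per year:

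| | Baseline | 1 month | 4 months | 7 months | 13 months |
|---|---|---|---|---|---|
| Falls window (months) | 12 | 1 | 3 | 3 | 6 |
| Expected falls | 1.00 | 0.08 | 0.25 | 0.25 | 0.50 |
| Hospitalization window (months) | 6 | 1 | 3 | 3 | 6 |
| Expected hospitalizations | 0.50 | 0.08 | 0.25 | 0.25 | 0.50 |

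Nothing changes in these people, yet the raw counts move by a factor of up to twelve. The distortion can also hide decline. If the fall rate doubles to two per year by the four-month contact, the expected count there is 2 × 3/12 = 0.50, still half the baseline 1.00. The rate would have to reach 1.00 / (3/12) = 4 per year before the raw count matched baseline. Table 1 gives no window for GP visits, so the same calculation cannot be done for them.

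**The case against.** **How many rows are affected.** A reader might infer that six of 13 outcomes are categories. The document does not support that. Services and supports carry a frequency as well as a type ("Greater type and frequency of use of formal community services or informal supports"). Carer engagement ("Increased carer involvement") could be yes/no or an amount, and satisfaction could be a rating score. Table 1 also mixes outcomes with independent variables without saying which is which. This limits the tally to at least five rows. It does not remove the problem, because all five appear among the criteria for functional decline.

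**How arbitrary the codes are.** A reader might also infer that the codes are wholly arbitrary and that renumbering could favour either arm. Study 1 analysis fixes the order for gait aid and living arrangements, so only the spacing is open. Simulating a two-sample comparison with no true difference (50 v 50, four categories, assumed shares), about 21% to 22% of trials changed verdict across all 24 numberings, but most of those numberings break the stated order. Across the three order-preserving codings above the figure was 6%, and any single coding kept its type I error at about 4% to 6%. One coding fixed in advance would therefore not inflate false positives. What remains is that the size of the effect, and the power to detect it, rest on a spacing that nobody has justified.

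**The yes/no route.** Nothing forbids analysing the change rules in Study 1 analysis, which are in effect binary and unaffected by recoding. That stands, but the analysis sentence speaks of change in each measure, not in the decline indicator, and ANOVA is still a weak model for a binary outcome.

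**Counts.** A claim that rate models are needed for power is not supported. In a simulation with assumed means of 1.0 v 0.5 and strong overdispersion, power was 42% for a comparison of means and 48% for a negative binomial model, whose type I error was 6.8% against 5.4%. The case for rates rests on the recall windows. The mention of a baseline rate suggests that rates are intended, but the analysis sentence does not say so. The windows are the same in all cohorts, so a cohort comparison at a single contact is not biased by them. The damage is to change over time, which is what the model is meant to estimate.

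**Conclusion.** The point holds in limited form and should be corrected. One means model is fixed for all outcomes and is mismatched to at least five of the 13 rows in Table 1. For the two ordered categories, the result depends on an unstated spacing; the 17% to 24% change in verdict is illustrative and rests on an assumed distribution and a true effect. For falls and hospitalizations, the distortion follows directly from the printed windows and needs no distributional assumption: at a constant rate, expected falls drop from 1.00 at baseline to 0.25 at four months. It assumes only that raw counts are what enters the model. The document does not support saying that six outcomes are categories, that the codes are entirely arbitrary, or that false positives are inflated. The iADL and SF12 analyses and the sample size of 100 are untouched.

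**What to change.** Reword the analysis paragraph as follows.

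- Limit the repeated measures model for means to the ADL, iADL, SF12 and AQoL scores.
- State the levels and order of gait aid, living arrangements and any other ordered multi-level measure, and analyse them with an ordinal repeated measures model such as proportional odds. Where levels are sparse, analyse the yes/no change rule from Study 1 analysis with a logistic model. At an assumed 5% in supported care, 50 per arm gives only 2 to 3 people at that level, too few for a stable ordinal fit.
- Analyse falls and hospitalizations as rates, using a negative binomial or overdispersed Poisson model with robust standard errors and log recall months as offset.
- State the recall window for GP visits, then treat them the same way.
- Say which rows of Table 1 are outcomes and which are independent variables.

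The cost is a little more programming, and odds or rate ratios in place of mean differences for these measures. Apart from stating the GP recall window, no change to data collection, visits or sample size is needed.

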### Hypotheses

As shown in Figure 2, our hypothese are:

1. The observed cohort will not demonstrate FD over the following 12 months in any FD measure.

2. The low SF12-MCS, no treatment cohort will demonstrate significant FD in any one or more outcome measures, taken over the next three months, when compared to their baseline recruitment status.

3. The low SF12-MCS, intervention cohort will show no FD (comparable findings to the observed cohort) over the next 12 months.

4. Additionally, those individuals in the low SF12-MCS, no treatment cohort who demonstrate significant FD at three months follow-up, and who access ‘rescue’ intervention (see Section on Ethics), will show an attenuated rate of FD over the following twelve months, compared with the rate they exhibited in the first three months.

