### Ethical issues

Written permission has been obtained from the Hospital Executive and ED Management of the research site, and ethical approval has been granted by the Human Research Ethics Committee of the University of South Australia (Application ID: 0000031475).

While there are indications from its early evaluation data that the ECH intervention is acceptable to clients, its effectiveness is largely unproven, particularly in individuals with low SF12-MCS scores at commencement. We do not know that the intervention will provide any advantage; in fact, individuals may perceive that they are subjected to additional burdens, such as unwanted assessments and visitors in their home for (perhaps) no overall benefit. We see no disadvantage for the ‘control’ group (low SF12-MCS, no treatment cohort) at this point in our understanding, in not being offered care, nor not knowing that the intervention is available, as they are currently not offered routine intervention so early after an ED discharge. If ,however, at subsequent follow-up points (three, six or twelve months), any participant in the observed cohort arm or the low SF12-MCS, no treatment arm is identified as potentially demonstrating FD on any study measure, the need for rescue care will be suggested and ways to access this discussed. This may include attendance at their GP or making contact with local community service providers.

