### Sample size considerations

To date, there is scant research that has established the effectiveness of any community-based person-centered intervention program that alerts older people who are on the cusp of FD to impending FD and provides means to assist and support them. We drew the likely effectiveness of the proposed intervention program from research on early intervention programs for at-risk older people who are in hospital or rehabilitation units. This included an Australian study [47] (significant improvement in goals and functioning) and a Dutch study [48] (effect size 0.25). We acknowledge that this research may not be readily generalizable to estimate effectiveness of the intervention in our reference population; however, it is the best available evidence for sample size calculation.

Our nested RCT study sample size was further calculated on minimal differences in iADLs and SF12 scores, expected at three-month follow-up from our pilot data [37]. These estimates are based on the three-month follow-up distributions for iADLs and SF-12. Parameters of power were set at π = 80% (1-β), with α = 5%. For iADLs, we identified that a minimum absolute effect size of 1.2 would be needed for participants to have dropped by at most 1 point on the Lawton scale (the Lawton definition of FD requires a drop of 2+ points on the scale). Thus, a minimum sample size of N_IADL_ = 50 per RCT cohort would be required (total 100). For the MCS domain of SF-12, a minimum absolute effect size of 4.3 would need to be observed, to put all scores above or equal to the median value, giving sample size of N_MCS_ = 30 per RCT cohort (total 60). Similarly for the PCS domain of SF-12, the minimum absolute effect size of 12.2 gives a sample size of N_PCS_ = 6 per RCT cohort (total 12). We require significance to be determined both clinically and statistically, so over-sampling is not of concern and, therefore, we choose the highest sample size (N_IADL_) of N = 50 per RCT cohort (100 total) at three months RCT follow-up (four months from ED recruitment). Thus, our continuing RCT sample at three months will reflect 100 individuals with low SF12-MCS (randomized 50 each into intervention and control arms), and 100 individuals with high SF12-MCS who will simply be followed-up.

To provide the nested RCT cohort sample, there are specific considerations which will influence the number of individuals invited to participate in Study 1:

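### Eleven functional decline (FD) criteria with no lead measure, judged by an any-measure standard, tilt H1 towards failure and H2 towards success by chance

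*Protocol article*

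**What the plan says.** All places are in the protocol article.

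- **Study 1 analysis.** The list opens with "FD will be assessed as change from baseline at each time point as" and has eleven bullets: falls, hospital or ED contacts, ADL, iADL, SF12, AQoL_4D, gait aid, living arrangements, carer involvement, community services or supports, and GP visits. Some have no minimum size, for example "Any decrease in AQoL_4D" and "More frequent GP attendances". No number of criteria, lead criterion or hierarchy is given.
- **Hypotheses.** H1: "The observed cohort will not demonstrate FD over the following 12 months in any FD measure". H2: the untreated low-MCS cohort "will demonstrate significant FD in any one or more outcome measures" over the first three months, against its own baseline. H3: the intervention cohort "will show no FD (comparable findings to the observed cohort) over the next 12 months".
- **Ethical issues.** The suggestion of rescue care applies when a participant in either non-intervention cohort "is identified as potentially demonstrating FD on any study measure". H4 concerns untreated participants who show FD and take up that care.
- **Sample size considerations.** The 50 per arm comes from an absolute iADL difference of 1.2, with a parenthesis that "the Lawton definition of FD requires a drop of 2+ points on the scale". Smaller numbers follow from the two SF12 components, and the largest is kept.
- **Analysis of data from Studies 1 and 2.** Each outcome measure is analysed by repeated measures ANOVA with contact point and cohort as factors.

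**The concern.** One decline on any of eleven measures is enough to contradict H1 and enough to support H2. Chance findings on the individual measures therefore accumulate, and they push the two hypotheses in opposite directions. H1 becomes hard to sustain even if the observed cohort is stable, while H2 can be met even if the untreated cohort is stable. H3 leans on the observed cohort as its no-FD standard, so a chance decline there also blurs what comparable findings would mean.

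This is separate from whether any one criterion is too loose, because it remains when each has a low error rate. Nor is it only a detail that an analysis plan could supply later: the any-measure standard is written into the hypotheses themselves. The article also does not say whether a cohort demonstrates FD through its mean or through individual members meeting a criterion, so both readings need checking.

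**Working it through.** The article gives no FD rate, no error rate per criterion and no combined error rate, so it has no figure of its own to reproduce on this point.

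**Inputs from the article**
- Criteria: 11 (Study 1 analysis).
- Contacts in the 12-month window: 3, at months 4, 7 and 13 after recruitment (Subject selection and randomization). H2 uses only the first of these.
- α = 5%, sidedness not stated (Sample size considerations).
- Observed cohort: 100 people (Sample size considerations).

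**Assumed inputs:** the false-flag rate p per criterion per contact, and the correlation between criteria.

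**1. Cohort-level reading, no true change**

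P(at least one false decline) = 1 − (1 − a)^k for k independent tests. Here a = 0.025 if tests are two-sided at 5% and only the harmful tail counts, and a = 0.05 if the full 5% lies on the side of decline.

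| Tests | a = 0.025 | a = 0.05 |
|---|---|---|
| k = 11 (one test per measure) | 1 − 0.975^11 = 24% | 1 − 0.95^11 = 43% |
| k = 33 (11 measures × 3 contacts) | 1 − 0.975^33 = 57% | 1 − 0.95^33 = 82% |

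The k = 11 row fits H2, which looks at one contact. It also fits H1 if each measure is tested once over the whole period. The k = 33 row fits H1 if every contact is compared with baseline. Positive correlation lowers all four figures.

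**2. Person-level reading, stable people**

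Independent criteria: 1 − (1 − p)^(11v) for v contacts. Correlated criteria: simulation of 40,000 people with a shared latent normal component. Share flagged at one contact / over three contacts:

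| p | Independent | Correlation 0.3 | Correlation 0.5 |
|---|---|---|---|
| 2% | 20% / 49% | 15% / 31% | 13% / 23% |
| 5% | 43% / 82% | 33% / 55% | 26% / 41% |
| 10% | 69% / 97% | 52% / 75% | 42% / 59% |

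If each criterion's result also persists in the same person between contacts (a further latent component of 0.4), the 41% falls to 35%. Under independence, more than half of stable people are flagged over three contacts only if p exceeds 1 − 0.5^(1/33) = 2.1%.

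**3. H1 read as nobody flagged**

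With p = 1%, one contact, independent criteria and 100 independent people, the probability is 0.99^(11 × 100) = 0.00002. In the table's mildest one-contact case (p = 2%, correlation 0.5, 12.7% flagged) it is (1 − 0.127)^100, about 0.000001.

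**4. What the trial was sized on**

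n per arm = 2(1.96 + 0.84)²·SD²/d². With d = 1.2, n = 50 is returned when SD = 2.14. That SD is solved backwards, because the article gives none. The form of the calculation is a difference in mean iADL score, not in a proportion with FD.

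**The case against.** The strongest reply is that no pooled any-of-eleven endpoint is analysed anywhere. The criteria list never says that one is enough, the planned ANOVA treats each measure separately, and H1 to H3 speak of cohorts. Figure 2, which illustrates the hypotheses, is not available here and might settle the level intended. FD is also presented as multi-domain, and combination and multiplicity rules often sit in an analysis plan.

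Much of this stands, and it rules out several stronger readings that a reader might infer.

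- **That most stable people would be classed as declining.** This depends on assumed rates and on independence. At 2% per criterion it is under half over three contacts even when criteria are independent, and at 5% with correlation 0.5 it is 41%.
- **That H1 must fail by arithmetic.** This holds only if H1 means that no individual is flagged. On cohort means it is inflated error.
- **That H3 fails in the same way.** H3 does not carry the any-measure wording, and its parenthesis allows a relative comparison with the observed cohort.
- **That the randomized comparison loses power by dilution.** That would need a pooled binary FD test, which the article does not plan.
- **That the trial was sized on the proportion falling 2+ points.** It was sized on a 1.2-point difference in score.

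The reply does not remove the core. The any-measure standard is stated in H1, H2 and the rescue wording, so it is not merely left open. Analysing each measure separately is what creates the 11 or 33 chances. H4 and the rescue wording do require individuals to be classified.

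**Conclusion.** The concern holds in limited form. Eleven criteria without a lead or a combining rule, together with an any-measure standard in H1 and H2, make H1 hard to sustain and H2 easy to meet by chance, and weaken the observed cohort as the reference for H3. At cohort level the chance of at least one false decline is 24% to 43% for 11 tests and 57% to 82% for 33. These are figures for independent tests, and correlation between measures reduces them. At person level the size rests on an assumed false-flag rate: at 5%, about 41% (correlation 0.5) to 82% (independent) over three contacts. Only H1 read as nobody flagged is practically unattainable whichever of these assumptions is used. The data collected are unaffected. What suffers is the conclusion that H1 to H3 can support.

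**What to change.** - **Lead measure.** In Hypotheses, judge H1 to H3 on change in total iADL score, the measure that set 50 per arm. Give the proportion falling 2+ points in total iADL as a supporting summary.
- **Other criteria.** Report the rest of the Study 1 analysis list separately as secondary, none able to confirm or refute a hypothesis alone.
- **H1.** Restate it as the estimated iADL change in the observed cohort, and its FD proportion, each with a 95% confidence interval.
- **H2.** Replace the one-or-more-measures condition with the lead measure at three months.
- **H3.** Restate it as between-cohort differences with 95% confidence intervals, in place of a claim of no FD.
- **Level of judgement.** Say whether each hypothesis concerns the cohort mean or individuals.
- **Rescue wording.** The any-study-measure phrase in Ethical issues, on which H4 depends, must be reconciled with Study 1 analysis and Hypotheses. Which clinical rule is right is not a matter for this review.

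The cost is rewording only, with no new data or visits. The downside is that decline outside iADL becomes secondary evidence, which narrows a concept that the authors meant to be broad.

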**Methods/Design:**

A randomized controlled trial (RCT) nested within a 13-month longitudinal cohort study. The RCT (conducted over 12 months) tests the effectiveness of a novel, early, home-based, personalized program (compared with no intervention) in arresting or slowing FD.

TRIIFL focuses on older adults living independently in the community, who have not yet had a serious health event, yet are potentially on the cusp of FD. Participants in the longitudinal cohort study will be recruited as they present to one large tertiary hospital Emergency Department, providing they are not subsequently admitted to a ward. Sample size calculations indicate that 570 participants need to be recruited into the longitudinal study, with 100 participants randomized into the trial arms.

Measures from all subjects will be taken face-to-face at baseline (recruitment), then subsequently by telephone at one, four, seven and thirteen months later. Measures include functional abilities, quality of life, recent falls, mobility dependence, community supports and health service usage. Specific to the nested RCT, the quality of life tool (SF12) applied at one month, will identify individuals with low mental component quality of life scores, who will be invited to enter the RCT.

Assessors will be blinded to RCT arm allocation, and subjects in the RCT will be blinded to the intervention being received by other subjects.

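### No hypothesis compares the two randomised arms: Hypotheses 2 and 3 set decline in one arm against no decline in the other, a pattern that an inert programme can produce

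*Protocol article*

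**What the plan says.** The abstract (Methods/Design) describes the RCT as a test of a "personalized program (compared with no intervention) in arresting or slowing FD". The section Sample size considerations has participants "randomized 50 each into intervention and control arms", with the number driven by iADL at three months: "For iADLs, we identified that a minimum absolute effect size of 1.2 would be needed".

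The section Hypotheses then lists four statements:

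- Hypothesis 1: the observed (high-MCS) cohort shows no decline over 12 months.
- Hypothesis 2: the untreated low-MCS arm "will demonstrate significant FD in any one or more outcome measures, taken over the next three months, when compared to their baseline recruitment status".
- Hypothesis 3: the low-MCS intervention arm "will show no FD (comparable findings to the observed cohort) over the next 12 months".
- Hypothesis 4: untreated participants who take up rescue care decline more slowly afterwards than before.

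Under Analysis of data from Studies 1 and 2, a separate repeated measures ANOVA is planned for every outcome. Its explanatory terms are described in this way: "with study contact point, cohort (1, 2, or 3) and key demographic features as independent variables". The text does not say which term or contrast carries the treatment comparison.

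**The concern.** Randomisation supports one inference: a difference between the intervention arm and the no-treatment arm. Hypotheses 2 and 3 never state it. Hypothesis 2 is a before-after test in one arm, and Hypothesis 3 is a finding of no decline in the other. A reader who sees both confirmed will conclude that the programme worked, although the arms have not been compared.

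Four features make this worse.

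- The windows differ: three months for Hypothesis 2, 12 months for Hypothesis 3.
- Hypothesis 2 counts change from recruitment in the ED. That is one month before randomisation, so its change includes a period that the programme cannot affect.
- The only comparator named in Hypothesis 3 is a cohort defined by a one-month MCS of 55 or more. It is not randomised, and no margin says how close counts as comparable. Failure to detect decline in about 50 people is not evidence of none.
- Hypothesis 3 demands no decline, while the abstract also counts slowing as success. A programme that slows decline without stopping it could fail Hypothesis 3.

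**Working it through.** **The plan's own figure.** The inputs are an iADL difference of 1.2, power 80%, α 5% and 50 per arm (Sample size considerations). No SD is given and the sidedness is not stated, so 50 cannot be reproduced directly. Solving back:

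- Two-sample, two-sided: n = 2(1.960 + 0.842)² SD² / 1.2² = 50 gives SD = 2.14, a standardised difference of 1.2/2.14 = 0.56.
- Two-sample, one-sided: SD = 2.41.
- One-sample (change within an arm), two-sided: n = (1.960 + 0.842)² SD² / 1.2² = 50 gives SD of change = 3.03.

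If the iADL SD is about 2.14, 50 per arm gives 80% power for the direct comparison of arms.

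**One measure, inert programme.** Both arms have the same true decline, and each within-arm test has power p to detect it. The arms contain different people, so the tests are independent:

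P(control significant, intervention not) = p(1 − p)

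- p = 0.5: 0.5 × 0.5 = 25%
- p = 0.8: 0.8 × 0.2 = 16%
- p = 0.2: 0.2 × 0.8 = 16%

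A two-sided 5% test between the arms wrongly favours the programme in 2.5%, whatever the common decline. The values of p are assumptions.

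**Several measures, strict reading.** Suppose Hypothesis 2 is met if any of 11 measures shows significant decline in the control arm, and Hypothesis 3 is met only if none does in the intervention arm. Eleven is the number of criteria under Study 1 analysis. Counting only declines (2.5% each), with independent measures and no true decline:

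- P(at least one in an arm) = 1 − 0.975¹¹ = 24.3%
- P(control at least one, intervention none) = 0.243 × 0.757 = 18.4%

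Simulation (20,000 trials per cell, 50 per arm, same true decline on every measure in both arms, normal test statistics) gives the chance that both hypotheses are met:

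| True decline (SD of change) | Correlation 0 | 0.3 | 0.5 |
|---|---|---|---|
| 0 | 18% | 15% | 13% |
| 0.1 | 21% | 25% | 24% |
| 0.2 | 2% | 12% | 19% |
| 0.28 | 0% | 3% | 7% |

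**Several measures, loose reading.** If it is enough that at least one measure is significant in control and not in intervention, the chance is 15–24% with no decline, 41–66% at 0.1 SD and 67–92% at 0.2 SD.

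**A check on the remedy.** In the same simulations, direct tests between arms on all 11 measures, with any one counting, favour the inert programme in about 15–24% of trials. The 2.5% therefore needs both the randomised contrast and a single named outcome.

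**The case against.** The strongest reply is that the comparison is in the document. The abstract names no intervention as the comparator, Aim 1 asks whether the programme reduces the likelihood or rate of decline, and the sample size is set per randomised arm. No sentence says that Hypotheses 2 and 3 together are the rule for declaring efficacy, and Figure 2, to which that section refers, is not available here. The three-month window of Hypothesis 2 may also have a reason, since rescue care can be suggested from that visit on. All of this stands. It shows that the authors intend the right comparison, not that the hypotheses state it.

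A reader might go further and infer several things that the documents do not support.

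- *That the three-cohort ANOVA is itself wrong, because high-MCS and low-MCS people differ and an overall test would reject for that reason.* The plan does not say which term is tested. A three-level factor allows the contrast between the two randomised arms. The model addresses change over time, so a constant gap between cohorts would not by itself produce a time-by-cohort effect. The term may be left to an analysis plan.
- *That pre-randomisation contacts dilute the effect to three fifths.* That holds only if a cohort main effect over all five contacts is the efficacy test, which the plan does not say.
- *That eleven criteria give a 43% false-positive rate.* 1 − 0.95¹¹ = 43% ignores direction and correlation. Counting declines only, it is 24% if the measures are independent and about 15% at correlation 0.5. The eleven items are also change criteria for Study 1, not a stated list of group-level tests, and a false positive in the control arm alone does not make the programme look effective.

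**Conclusion.** The point holds for the hypotheses. They leave out the one comparison that the RCT was set up to make, and Hypotheses 2 and 3 can both be met by a programme that does nothing. This is more than detail left to an analysis plan: a plan faithful to these hypotheses would inherit the fault, and one that compared the arms would depart from them.

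The size is conditional. The 16–25% against 2.5% is a single-measure illustration at assumed within-arm power of 50% to 80%. With 11 measures on the strict reading it is about 13–25% for true declines of 0 to 0.1 SD, falling towards zero when decline is large on every measure. The loose reading gives more. The protocol gives neither the correlations nor the expected declines, and does not say which reading applies, so no single figure can be claimed.

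The ANOVA is unspecified on this point rather than wrong. What must not happen is that an overall three-cohort test is read as the treatment effect.

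**What to change.** Restate the primary RCT hypothesis as intervention versus no treatment on mean iADL score three months after randomisation (four months after recruitment), the outcome and visit that already set the sample size. Analyse participants as randomised, adjust for the one-month value, and estimate the effect either in the two randomised arms alone or as a prespecified contrast within the three-cohort model.

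Make the 12-month results and all other outcomes secondary, reported with estimates and intervals. Use the observed cohort for the screening part of Aim 2 (whether low MCS identifies incipient decline) and for description. Drop absence of decline, and likeness to the observed cohort, as evidence of efficacy.

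The cost is rewording: no new data, visits or participants. The downside is that claims on outcomes other than three-month iADL become secondary. The iADL SD should also be stated, since 80% power at 50 per arm rests on a value of about 2.14.
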